### Statistical analyses and reporting

Due to the wide scope of the study, analyses and reporting will be conducted in several dedicated subprojects. These will be organized along the main hypotheses, the main topics mentioned under “Effectiveness and process evaluations ”, and the time frame of the study. A detailed analysis plan and a publication and dissemination plan will be prepared for each subproject. An initial data analysis will be performed according to the recommendations of the STRATOS (STRengthening Analytical Thinking for Observational Studies) initiative [75], informing all subprojects about the available meta data, the patient flow in the project and the distribution of key variables. Across all sub projects we will make use of hierarchical models to take the hierarchical structure (clinics and clinicians within clinics) into account. Latent class models will be used to detect patient and clinician profiles and structural equation models will be used to investigate the associations among latent variables. Mediation analysis will be performed according to the causal framework described by Vanderweele [76]. The overall research team takes the responsibility to prepare an additional publication summarizing the results of the different subprojects.

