Second, the main body of the course is aimed at developing participants’ ability to deliver the GLA:D Back clinical intervention as a way of addressing pain cognitions and behaviours by introducing all elements of the clinical intervention: goal-setting, clinical tests, patient education and supervised exercises. Goal-setting is introduced by presenting the SMART-model (Specific, Measurable, Acceptable, Realistic, and Time bound goals) [40]. Role plays to practice the use of explanatory models and skills training are used to become familiar with pain education, physical tests and exercises. Using some of the slides from the patient education material, participants work in groups taking turns to deliver key messages from the pain education to each other as they would in a real patient session, evaluated using peer feedback. The clinical tests and exercises are introduced in a practical session where tests are carried out on a colleague, and exercises are performed by the participants while examples of variations are presented. The supervision of exercises is practised in a session based on video cases and centred on the messages (spoken and unspoken) that can be delivered while supervising patients in the clinic. Key messages from the patient education should be reinforced during the instruction of exercises, for example, when explaining to patients how to cope with pain provocation during exercises rather than withdrawing from the activity. Finally, participants are introduced to the clinical registry used for data entry. At the end of Day 2, clinicians plan how and when to start GLA:D Back in their clinics. They are encouraged to pursue implementation by referring to the success of the GLA:D Knee/Hip model and the experience with GLA:D Back from pilot testing, as well as by emphasising the importance of physiotherapists and chiropractors taking on the role of ensuring access to evidence-based care for back pain.

Courses may be refined during the process of implementation, however, the core parts that are not subjects to change are: 1) familiarising participants with the key messages of the clinical intervention, 2) the introduction to the clinical registry, and 3) that the clinicians practice the delivery of patient education and the instruction of exercises during the course.

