#### Evaluation of the clinician educational intervention

All clinicians participating in a course will be included in this evaluation. The course content and delivery will be evaluated via observations by an expert in medical education to confirm that the planned learning activities are delivered. Outcomes of learning activities (Table 1) will be compared between courses and any trends in change over time described.

Evaluations of clinician-level outcomes will be investigated in an observational longitudinal design with clinician-reported data collected before the clinician training course, immediately after the course and 5 months later, and with patient-reported information on delivery collected at their three-months follow up. Changes over time in treatment orientation and confidence in managing patients with LBP will be described, and potential relationships between clinician characteristics, treatment orientation and confidence will be determined.

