### Sample size

The study population will be the clinicians who complete GLA:D Back courses during 2018 and the patients enrolled in GLA:D Back by these clinicians during a 6-months window of inclusion commencing after a 3-month phase of familiarisation with the program after the course. Assuming that clinicians from 150 clinics will participate in the GLA:D Back course during 2018, and they enrol 1500 patients during the study period, we will have 90% power to demonstrate pre-post comparison changes at the patient level with an effect size of 0.2 while accounting for clustering within clinics and clinicians up to a variance inflation factor of 5. At the clinician level, we will have [75]90% power to demonstrate changes with an effect size of 0.27.

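### The clustering structure named for all subprojects leaves out the training course, so the standard error of the mean clinician change may be understated

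*Protocol article*

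**What the plan says.** The protocol article makes one modelling commitment for the whole study. Under Statistical analyses and reporting it writes "Across all sub projects we will make use of hierarchical models", and the same sentence lists the levels: "hierarchical models to take the hierarchical structure (clinics and clinicians within clinics) into account". No section treats the course as a random effect, a fixed effect or a cluster. The same paragraph defers detail: "A detailed analysis plan and a publication and dissemination plan will be prepared for each subproject".

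Other sections describe the course as something that can vary:

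- The clinician educational intervention (Interventions): training is a two-day course with group work, and "Courses may be refined during the process of implementation". Certain core parts may not change.
- Study objectives (end of Background): one aim is to monitor learning outcomes and adapt course delivery in response.
- Evaluation of the clinician educational intervention: outcomes of learning activities "will be compared between courses and any trends in change over time described". Clinicians are followed before the course, directly after it and 5 months later, with no untrained comparison group.

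Sample size begins "Assuming that clinicians from 150 clinics will participate in the GLA:D Back course during 2018" and allows a variance inflation factor of up to 5 for patients. For clinicians it claims "90% power to demonstrate changes with an effect size of 0.27", with no number of clinicians and no clustering allowance.

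**The concern.** Clinicians who attend the same course share teachers, materials, group exercises and the version of the course then in use. Their changes in treatment orientation and confidence may therefore be correlated, including between clinicians from different clinics. A model with clinic and clinician terms treats clinics trained together as independent. The plan recognises course as a possible source of variation when it describes outcomes, but not when it sets the structure for inference.

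One objective is to determine whether orientation and confidence change after the course. If course-level variance in that change is above zero and is left out, the interval around the mean change is too narrow and a test of it rejects too often.

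**Working it through.** **Inputs from the protocol article.** 150 clinics (Sample size). A minimum of 300 clinicians trained in 2018, 60 in each of five regions (Table 2). 90% power at an effect size of 0.27 for clinicians (Sample size).

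**Assumptions, not in the document.** 300 clinicians analysed; m_k = 2 per clinic (300/150); clinic ICC of the change score ρ_k = 0.05; clinics nested in courses; 20 courses of 15 or 10 courses of 30; course ICC ρ_c from 0 to 0.05; two-sided 5% level; large-sample normal test.

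**Step 1: the stated clinician-level power.** For a paired change, n = ((1.960 + 1.282)/0.27)² = 144, or 147 with the t distribution. An effective sample of 150 gives 91.1% power (90.7% with t), so the figure reproduces at about 150 independent units. With 300 independent clinicians power would be 99.7%. The figure therefore fits either about 150 clinicians or 300 with a variance inflation of about 300/144 = 2.08. The document does not say which.

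**Step 2: variance of the mean change.**

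- Clinic-only factor: V₁ = 1 + (m_k − 1)(ρ_k + ρ_c). The fitted clinic term absorbs the course covariance within a clinic.
- Full factor: V₂ = V₁ + (m_c − m_k)ρ_c, where m_c is the number of clinicians per course.
- Ratio of true to clinic-only standard error: R = √(V₂/V₁).
- Actual error rate of a nominal 5% test: 2(1 − Φ(1.96/R)).

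Worked case, 10 courses of 30 with ρ_c = 0.05: V₁ = 1 + 0.10 = 1.10; V₂ = 1.10 + 28 × 0.05 = 2.50; R = √(2.50/1.10) = 1.51; error rate 19%.

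| Course ICC | 20 courses of 15: V₁, V₂ | R | Type I error | 10 courses of 30: V₁, V₂ | R | Type I error |
|---|---|---|---|---|---|---|
| 0 | 1.05, 1.05 | 1.00 | 5% | 1.05, 1.05 | 1.00 | 5% |
| 0.01 | 1.06, 1.19 | 1.06 | 6.4% | 1.06, 1.34 | 1.12 | 8.1% |
| 0.02 | 1.07, 1.33 | 1.11 | 7.9% | 1.07, 1.63 | 1.23 | 11.2% |
| 0.05 | 1.10, 1.75 | 1.26 | 12% | 1.10, 2.50 | 1.51 | 19% |

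The comparison is with the clinic-level model that the article names, not with full independence.

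**The case against.** The strongest reply is that the clause is a one-line general commitment in a condensed article. It does not exclude further terms, and each subproject is to have its own analysis plan, where random effects and degrees-of-freedom methods normally belong. This stands in part: the structure is named rather than closed, and a later plan could add course. But the article is not merely silent. It states one structure for every subproject, and plans that inherit it would inherit the gap.

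Second, course is not ignored: learning outcomes will be compared between courses, and core course parts are protected from change. That is true, but a descriptive comparison does not correct the standard error of the overall change.

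Third, the study population is the clinicians who completed courses in 2018. If inference is confined to the courses held, course-level variation need not count as sampling error. This is a legitimate choice. However, the Discussion wants the results to help develop implementation strategies, which reaches beyond those courses.

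Fourth, a reader might infer that associations of clinician factors with orientation and confidence are affected in the same way. The document does not support that. For a covariate the inflation is roughly 1 + (m_c − 1) × ICC of the covariate × ICC of the outcome. Age, sex, profession and experience vary within courses, so it may be close to 1.

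Finally, the article does not say that teaching staff differ between courses, nor that colleagues from one clinic attend the same course. Course may therefore be crossed with clinic instead of lying above it.

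**Conclusion.** The point holds in conditional form. The named structure omits the level at which the education is delivered, and a clinic effect cannot carry covariance between clinics trained together. Under the assumptions shown, the true standard error of the mean clinician change is 1.06 to 1.26 times the clinic-only value with 20 courses of 15, and 1.12 to 1.51 times with 10 courses of 30.

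A reader might go further and conclude that the standard errors are too small as a matter of fact. The document does not support this, because it gives no course number, size or ICC, and at an ICC of 0 nothing is lost. It would also be too much to say that the education hypothesis rests on an invalid test. That hypothesis concerns preparing clinicians to deliver the intervention as intended, while change in orientation and confidence is a separate objective, assessed as an uncontrolled pre-post change with no stated significance level.

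Nor can a power shortfall be claimed. If 300 clinicians underlie the 0.27 figure, total variance inflation up to 2.08 is already covered, and only the last case in the table (2.50) exceeds it. If the basis is 150 clinicians, there is no such margin. This is an inexpensive improvement to make before analysis, not a fatal flaw.

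**What to change.** Under Statistical analyses and reporting, add course to the stated structure for the clinician-level change analyses. Use a random effect, or a fixed effect if courses are few, and say in the latter case that inference is to the courses held. Cross course with clinic if colleagues attended different courses. Apply a small-sample degrees-of-freedom correction (Satterthwaite or Kenward-Roger), because courses will be far fewer than clinicians, and report the course variance component.

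As a secondary clarification, state under Sample size the number of clinicians and the clustering allowance behind the 0.27 figure.

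The cost is one model term, using course attendance that course registration should already hold, and slightly wider intervals.

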## Discussion

This implementation-effectiveness study is designed to evaluate the process and outcomes of implementing a standardised intervention, GLA:D Back, for people with persistent or recurrent LBP. The implementation strategy targets clinicians and the clinical intervention targets people seeking care for persistent or recurrent LBP who are in need of improved self-management. In this study, we will investigate how standardised evidence-based care for LBP can become widely available, how the intervention will be delivered and to whom, what outcomes patients achieve in clinical practice, and what the effects will be at the national level. Further, we investigate potential mechanisms for effects by evaluating changes in several intermediate outcomes based on theoretical models for introducing behaviour changes and for supporting self-management of back pain.

The implementation strategy with a 2-day course for clinicians mirrors that of the GLA:D program for patients with knee and hip pain [31]. That program has achieved very large national adoption and has developed into an international model of standardised care with training of clinicians in Canada, Australia and China within only 5 years of its commencement [77, 78]. Organisations and clinicians have subsequently called for a similar model for back pain care and thus, GLA:D for knee and hip pain serves as a model for the implementation of evidence-based back pain care. A pilot study testing the feasibility of GLA:D Back showed good promise for implementation (nine test sites all enrolled patients in the GLA:D Back program within 2 months of clinicians’ course participation and clinicians’ and patients’ perceptions were positive) (manuscript in preparation).

Despite good intentions, implementation of health care initiatives is complex, a lot of factors affect implementation and very many aspects deserve evaluation. Therefore, implementation is best understood within a theoretical framework and should be planned and evaluated within one [79]. We will use the Behavior Change Wheel, which describes interventions and policies related to change of behaviour [35]. This framework facilitates a focused evaluation and also clarifies aspects of supporting behavioural change that our implementation strategy does not include. For example, we did not involve decisions-makers in health care from the beginning of the project and are aware that the existing reimbursement structure may be an important barrier to implementation.

This study initiates a line of research with the potential to generate insight into real life effects of recommended treatments for people with persistent or recurrent LBP, and into ways to assist clinicians in delivering this care. The clinical registry will continue after the study period and will generate a cohort for future monitoring of outcomes, as well as for embedded trials for testing alterations to the education of clinicians and to the clinical intervention. Educational interventions for clinicians using a workshop format with didactic and interactive elements have been used for implementation of guidelines on back pain [80] and osteoarthritis [81], but the amount and type of training needed for clinicians to deliver a new intervention with satisfactory fidelity is unknown. Thus, the effects of a more comprehensive training of clinicians is one aspect that can be tested in a future embedded trial. Also, the investigations of intermediate outcomes may inform alterations to the clinical intervention that can then be tested for effectiveness in a nested study.

Some compromises were made in the design of this study. First, given the large evidence base for patient education and exercise, we did not aim at a further evaluation of the clinical intervention in a randomised design. Instead, we focused on the implementation of such an intervention and an investigation into how delivery of care can be optimised in clinical practice. However, also an evaluation of the educational intervention for clinicians or the overall implementation could also have been undertaken in a cluster-randomised design. Unfortunately, due to the nationwide spread of the existing GLA:D knee and hip program and the high expectations associated with its extension to low back pain patients, a randomisation at the level of clinics or regions would not have met wide acceptance, and we did not adopt that design. Pragmatically, we investigate the effect of the clinical intervention itself only by a pre-post comparison among the participating patients. We originally planned to include at least a pre-post comparison based on two cross-sectional samples drawn from each clinic prior to, and after, introducing GLA:D Back. However, as the intervention will also change the composition of the patient population approaching the clinics, it was not possible to define a relevant patient group that would have resulted in comparable pre and post populations.

Another challenge in evaluating self-management interventions is the choice of outcomes. Of course, for long-term outcomes at the patient and societal levels, we could use established instruments and indicators. However, our aim is also to understand the intermediate process in reaching a long-term improvement, i.e. how a better self-management is reached and how it affects the long-term outcomes. The construct of self-efficacy is relatively well-defined and related measurement tools exist. More challenging is the measuring of self-management. It is not clear what defines the ability to self-manage and a large number of different tools and constructs have been used for measuring aspects of this [66]. As part of this study, we will investigate mechanisms behind the development of self-efficacy and self-management by testing hypothesised pathways and by combining quantitative and qualitative data to improve our understanding of patients’ perceptions of self-management.

In conclusion, this hybrid implementation-effectiveness study will evaluate efforts to implement a program aimed at promoting self-management of persistent and recurrent back pain in people presenting in Danish primary care and demonstrate what the actual target group is for this type of care and the outcomes achieved. This will help to develop strategies for implementing evidence-based care for back pain and potentially other musculoskeletal pain conditions.

### Organisation

The study is conducted by University of Southern Denmark, Department of Sports Science and Clinical Biomechanics. An advisory board is informed about study plans and progress and provides input but has no authority over project activities. University of Southern Denmark holds the GLA:D® trademark.

## Abbreviations

ASES: Arthritis Self-Efficacy Scale
BCW: Behaviour Change Wheel
B-IPQ: Brief Illness Perceptions Questionnaire
DIBQ: Determinants of Implementation Behaviour Questionnaire
DPA: Danish Data Protection Agency
GLA:D: Good Life with osteoArthritis in Denmark (only the acronym is used in GLA:D Back)
GP: General Practitioner
LBP: Low back pain
OPEN: Odense Patient data Explorative Network
PABS: Pain Attitudes and Beliefs Scale
PCS: Practitioner Confidence Scale
RCT: Randomised Controlled Trial
